### Study purpose

This study will explore the impact of a parent coaching intervention, with parent and child outcomes, on promoting healthy behaviours among the dyad. Specifically, this research aims to identify the impact of a coaching plus health education intervention compared to health education only on: (a) the PA levels of children (ages 2.5–10) and their parents with overweight/obesity; (b) the dietary intake of children and their parents with overweight/obesity; (c) parental motivation to engage in healthy behaviours; and (d) parental perspectives on how the program has impact on their and their child’s nutrition and PA behaviours. These primary outcomes will be measured via in-person parent interviews, parent and child 7-day step count and 24 h dietary intake, and standardized and validated questionnaires. Due to children’s active growth periods, PA and nutrition behaviours can be better predictors of health than anthropometric indicators [54]. Secondary outcomes will be measured by assessing: (a) parental BMI (calculated by measuring weight in kg, over height in m^2^); (b) parents’ overall perception of health; and (c) parents’ psychosocial variables (i.e., social support, self-esteem, and self-efficacy).

The research team hypothesizes that immediately following and at 6 months post-intervention, the coaching plus education group will report higher levels of parent-child PA, greater improvements in parent-child dietary intake choices, greater parental psychosocial benefits, and greater improvements in parents’ BMI values, compared to those who receive education only. The research team predicts that parents from higher socioeconomic status (SES) backgrounds will be impacted more favorably than those from lower SES backgrounds, as researchers have found greater difficulties associated with affecting behaviour change within lower SES environments [20]. It is also hypothesized that male parents and children will have higher PA levels, while female parents and children will have greater dietary intake improvements, and female parents’ psychosocial health will be impacted most positively, given that previous research has found young males tend to be more active than their female counterparts, and obesity affects psychosocial health of women more negatively than men [27].

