### Data analysis

SPSS (version 24) will be used to conduct a repeated measures MANCOVA to assess differences within groups, and a two-way ANCOVA to assess differences between groups, where baseline data will be the covariate, with differences analyzed using the post-hoc Least Square Differences method. As socioeconomic status (SES) has an impact on nearly all health issues, including obesity, and understanding its impact in the proposed project is necessary, a general linear model utilizing SES as covariate will be completed. Classification for SES will be based on education and low income cut off scores (LICO) utilizing Statistics Canada’s definition. The semi-structured interview responses from parents, to determine changes in family health behaviours and overall program experiences, will be analyzed in NVivo by two independent researchers. Inductive content analysis (a method in which patterns, themes, and categories emerge from the data, without an existing framework; [76]) will be employed to identify feedback themes. This process involves open coding, in which data is read through several times, and as many headings as necessary are written down to describe all aspects of the content [77]. The headings are then collected on a coding sheet, and categories are grouped and sorted into higher order headings [78, 79]. Data are classified into groups in order to help describe a phenomenon, increase understanding, and generate knowledge [80]. Once categories are decided upon, the two researchers compare headings and come to consensus on final themes, with the support of NVivo software.

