### Strengths and limitations

In contrast with previous parent-child interventions, to the best of the researchers’ knowledge, this is the first study that will evaluate the impact of Co-Active coaching and/or education on the family unit, via parent and child outcome measures. The use of mixed methods (i.e. using both qualitative and quantitative measures) ensures that the researchers will gain an in-depth understanding of participants’ experiences with both the program and process of developing healthy behaviours. In addition, the randomized controlled trial design, use of a comparison group, and incorporation of several previously validated tools also serve as strengths in this study. Interventions that are based on the foundation of health promotion (i.e. enabling individuals to improve and increase control over their own—and in this case, their family’s—health [81]) have been shown to result in successful behaviour change [35]. This program employs education and coaching, both of which encourage participants to develop skills that will allow them to increase control over their health decisions and environments [82]. Another strength of the study is the selected coaching method in that all CPCCs involved are trained in the same manner; meaning participants in the coaching group are receiving similar strategies to help target their areas of concern [82].

A limitation of this study may be the number of participants who do not complete the program; researchers have reported participants in control conditions of lifestyle interventions are more likely to drop out [82, 83]. To counteract this, and encourage full participation, the researchers remain in contact with participants throughout the study (via email reminders to complete assessments, and in-person follow-ups). A further limitation of this study may be low participation of fathers; a review examining the involvement of fathers in pediatric obesity treatment and prevention programs with parental involvement outlined that, out of 213 included RCTs, only 6% of participants were fathers [84]. The researchers are recruiting parents using many different methods, in hopes of reaching both mothers and fathers.

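### The SES prediction, if it concerns the coaching effect, is not tested by the stated model, which enters SES only as a covariate

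*Protocol article*

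**What the plan says.** In Background, Study purpose, the protocol article predicts that "parents from higher socioeconomic status (SES) backgrounds will be impacted more favorably than those from lower SES backgrounds". The reason given is that behaviour change is harder to bring about in lower-SES settings.

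Methods, Data analysis, lists three quantitative analyses: a repeated measures MANCOVA for within-group differences, a two-way ANCOVA with the baseline value as covariate for between-group differences, and, for SES, "a general linear model utilizing SES as covariate will be completed". SES is to be classified from education and low income cut-off (LICO) scores. No arm-by-SES term and no comparison of the arms by SES level is stated.

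The same Study purpose paragraph makes three predictions about sex: "male parents and children will have higher PA levels"; "female parents and children will have greater dietary intake improvements"; and "female parents’ psychosocial health will be impacted most positively". Data analysis does not mention sex, and it does not name the two factors of the two-way ANCOVA.

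The sample size section covers one question only, a two-group difference: 50 dyads, d = 0.8, 79% power, alpha 0.05.

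**The concern.** The SES sentence follows hypotheses that compare coaching plus education with education alone, and its rationale is how readily an intervention changes behaviour. Read that way, it says that the response to coaching depends on SES. The model named for SES holds the coaching effect constant across SES, so hypothesis and analysis do not match.

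This is more than missing detail. The article regards understanding the impact of SES in this project as necessary, and it then fixes a model that leaves this question unanswered. An analyst who follows the text would obtain an SES coefficient. A report could then present that coefficient as support for the prediction, although it shows only that SES is associated with the outcome. What is at stake is a stated hypothesis. The arm comparison does not depend on it.

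**Working it through.** **1. What each model estimates.** Let Y be the follow-up outcome.

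- Model as stated: Y = b0 + b1·baseline + b2·arm + b3·SES. The coaching effect is b2 at every SES level, and b3 is the SES association averaged over the arms.
- Model that addresses the prediction: Y = b0 + b1·baseline + b2·arm + b3·SES + b4·(arm × SES). The coaching effect is b2 + b4·SES, and b4 measures how it changes with SES.

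Invented cell means, in SD units of improvement, show that b3 and b4 answer different questions (two SES levels of equal size).

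| Scenario | Lower SES: control, coaching | Higher SES: control, coaching | SES coefficient | Difference in coaching effect |
|---|---|---|---|---|
| A | 0.0, 0.4 | 0.4, 0.8 | 0.6 − 0.2 = 0.4 | 0.4 − 0.4 = 0 |
| B | 0.4, 0.4 | 0.0, 0.8 | 0.4 − 0.4 = 0 | 0.8 − 0.0 = 0.8 |

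In A the SES coefficient is clearly positive, yet coaching works equally well in both strata. In B coaching works only in the higher stratum, yet the SES coefficient is zero.

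**2. The article's own power figure.** Inputs: 50 dyads and d = 0.8 (sample size section), 1:1 allocation (Abstract, Methods), so 25 per arm; two-sided alpha 0.05 (sidedness is not stated). Noncentrality = 0.8/√(2/25) = 2.83 with 48 df, which gives power 79.1%. The stated 79% reproduces, but it applies to the two-arm comparison alone.

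**3. Power for the added term.** The SES distribution is not given, so the split is an assumption. With SD 1 and per-arm subgroup sizes na and nb, SE = √(2/na + 2/nb), on 46 df.

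- Even split: na = nb = 12.5, SE = √(4/12.5) = 0.566. For an interaction of 0.8 SD, noncentrality = 0.8/0.566 = 1.41 and power = 28%. For 0.4 SD, power is about 11%.
- 30/70 split: SE = √(2/7.5 + 2/17.5) = 0.617; power for 0.8 SD is 25%.
- 20/80 split: SE = √(2/5 + 2/20) = 0.707; power for 0.8 SD is 20%.

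At an even split, 79% power is reached only for an interaction of 1.6 SD. Detecting 0.8 SD with 79% power would take about 194 dyads. The 95% CI half-width at N = 50 is 2.013 × 0.566 = 1.14 SD.

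**4. Allowance for baseline adjustment.** The figures above take no gain from the baseline covariate. If baseline and outcome correlate at r, the SE shrinks by √(1 − r²). The article gives no r. At an assumed r = 0.5 the SE is 0.566 × 0.866 = 0.490 and power for 0.8 SD is about 36%; at r = 0.7 it is 0.566 × 0.714 = 0.404 and about 49%. Even then the test stays far below the 79% used for the main comparison.

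**The case against.** The strongest reply is that effect modification is an interpretation. The article says that higher-SES parents will be affected more favourably; it does not say that the difference between coaching and education will vary by SES. Both arms receive the six education sessions, and the rationale concerns behaviour change in general. If the sentence means only that higher-SES parents improve more whichever arm they are in, an SES term in a baseline-adjusted model does address it. This stands in part. It is why the fix offers rewording as an alternative, and why it would be too strong to call the covariate model the opposite of a test. The wording still has to be settled, because the two readings need different models.

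A reader might also infer that the plan predicts better coaching results in females generally and leaves that untestable. The document does not support this. Females are favoured for diet and for parental psychosocial outcomes, while males are predicted to have higher PA levels, which is worded as a sex difference in level. The factors of the two-way ANCOVA are not named, so sex could be one of them. No wrong rule for sex is stated, and an article may leave such terms to a fuller plan. Nor does the article plan any sex-subgroup testing, so a warning about p-values from tiny subgroups would be speculation.

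It is also tempting to compute the number of fathers from the statement that "only 6% of participants were fathers": 0.06 × 50 = 3. That share comes from a review of other trials. The article gives no share for its own enrolment and describes efforts to recruit fathers, so the figure is only an illustration.

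Finally, an added term with low power will not settle the hypothesis. That is true, and it is the reason to label the result exploratory. It does not make the covariate coefficient an answer to the question.

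**Conclusion.** The point holds for SES. If the prediction concerns the coaching effect, the stated model cannot show whether that effect differs by SES, and a significant SES coefficient would not be evidence that it does. This rests on the form of the model and on no numerical assumption.

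The power figures only support the exploratory label. For a 0.8 SD interaction with 50 dyads, power is about 28% at an assumed even split and lower at uneven splits, before any gain from baseline adjustment.

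The sex predictions are secondary. No stated analysis names sex, but this is an omission that a fuller plan could fill, and it does not carry the point.

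The change should be made before analysis. It does not affect the validity of the main arm comparison.

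**What to change.** 1. State which meaning is intended. If the coaching effect is expected to be larger in higher-SES parents, add an arm-by-SES term to the baseline-adjusted outcome model, using one SES variable chosen in advance from the education and LICO classification. Report the interaction estimate with its 95% CI, label it exploratory, and say that the SES main effect will not be read as evidence on this hypothesis.
2. If the prediction means only that higher-SES parents improve more in both arms, reword it that way. The covariate term can then stay.
3. For sex, say which predictions concern the coaching effect and handle those in the same way, naming parent or child sex for each outcome. Describe differences by parent sex without testing them if few fathers enrol. Word the male PA prediction as a descriptive difference.

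The cost is one model term for SES, similar terms for sex if they are wanted, and some rewording. No new data should be needed: the SES classification is already planned, and demographic forms for parent and child are completed at baseline. The downside is an openly imprecise estimate, with a 95% CI of roughly ±1.1 SD under the even-split assumption without baseline gain.

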## Discussion

This protocol paper has detailed a methodological account of a comprehensive study, aimed at exploring the impact of a parent education compared to education plus coaching intervention, with parent and child outcomes, on promoting healthy behaviours among the parent-child dyad.

The increasing rate of overweight/obesity, and the associated adverse health conditions, in increasingly younger populations creates the need for the research outlined in this paper. Given that parents are a primary influence for their children’s PA and nutrition behaviours [1], interventions that support parents in making healthy choices should be explored and promoted further.

### Strengths and limitations

In contrast with previous parent-child interventions, to the best of the researchers’ knowledge, this is the first study that will evaluate the impact of Co-Active coaching and/or education on the family unit, via parent and child outcome measures. The use of mixed methods (i.e. using both qualitative and quantitative measures) ensures that the researchers will gain an in-depth understanding of participants’ experiences with both the program and process of developing healthy behaviours. In addition, the randomized controlled trial design, use of a comparison group, and incorporation of several previously validated tools also serve as strengths in this study. Interventions that are based on the foundation of health promotion (i.e. enabling individuals to improve and increase control over their own—and in this case, their family’s—health [81]) have been shown to result in successful behaviour change [35]. This program employs education and coaching, both of which encourage participants to develop skills that will allow them to increase control over their health decisions and environments [82]. Another strength of the study is the selected coaching method in that all CPCCs involved are trained in the same manner; meaning participants in the coaching group are receiving similar strategies to help target their areas of concern [82].

A limitation of this study may be the number of participants who do not complete the program; researchers have reported participants in control conditions of lifestyle interventions are more likely to drop out [82, 83]. To counteract this, and encourage full participation, the researchers remain in contact with participants throughout the study (via email reminders to complete assessments, and in-person follow-ups). A further limitation of this study may be low participation of fathers; a review examining the involvement of fathers in pediatric obesity treatment and prevention programs with parental involvement outlined that, out of 213 included RCTs, only 6% of participants were fathers [84]. The researchers are recruiting parents using many different methods, in hopes of reaching both mothers and fathers.

## Conclusion

All of the pertinent information necessary to develop and implement a parent-child intervention has been addressed including study design, population rationale, recruitment methods, outcome measure descriptions, intervention procedures, and data collection and analysis. The expected findings from this research will provide important insights into the impact of coaching on parents with overweight/obesity, and its applications to the family unit. From conducting this study, the researchers aspire to learn effective methods to support parents and children in developing and maintaining positive nutrition and PA habits. If effective, this intervention approach can be applied more broadly through public health interventionists to parent and child populations in hopes of reducing obesity-promoting behaviours within both individuals and their families. This program is currently on going; the researchers’ intention and goal is to make the results available, via peer-reviewed publications, in 2019.

## Abbreviations

BMI: Body Mass Index
CVD: cardiovascular disease
ESES: Eating Self-Efficacy Scale
GSE: Generalized Self-Efficacy (Scale)
IPAQ: International Physical Activity Questionnaire
LICO: Low-income cut off scores
MSPSS: Multi-dimensional Scale of Perceived Social Support
MVPA: moderate-to-vigorous physical activity
PA: Physical activity
RSE: Rosenberg Self-Esteem Scale
SF-36: Short-Form 36
TSRQ: Treatment Self-Regulation Questionnaire
WEL: Weight Efficacy Lifestyle (Questionnaire)
